# Study protocol (main points)

# The nutrition-based comprehensive intervention study on childhood obesity in China

Objective

The main purpose of the intervention study is to evaluate the feasibility and effectiveness of the comprehensive intervention program for childhood obesity which combined nutrition education and physical activity interventions. The second purpose of the intervention study is to compare the cost-effectiveness of the comprehensive intervention strategy with two other interventions, one only focuses on nutrition education, the other only focuses on physical activity. The final aim of the study is to raise the awareness of the national childhood obesity prevention and control policy recommendations

Study design

The study will be designed as a multi-centred randomiised controlled trial, which included 6 centres located in Beijing, Shanghai, Chongqing, Shandong province, Heilongjiang province and Guangdong province. Both nutrition education and physical activity intervention will be implied in all intervention schools of 5 cities, while in Beijing, nutrition education intervention will be implied in 3 schools and physical activity intervention among the other 3 schools. Nothing will be done in control schools.

Participants

A total of 9750 primary students (grade 1 to grade 5, aged 7-13 years) will participate in baseline and intervention researches of questionnaire, physical examination, physical quality test and blood biochemistry and so on. The study design in each center is presented in Figure 1. The method of two-step cluster sampling will be adopted. The first step is that randomly selected 6 schools from each centre assigned to either intervention (3 schools) or control condition（3 schools）. The second step is that randomly choose 2 classes from each grade, totally, around 250 subjects will be randomly selected from each school.

Figure 1 Study design in each center

Sample size calculations

The variable used for the calculation of sample size is the BMI changes. To detect a difference of 0.7 kg/m2 of BMI changes between the intervention and control groups, the minimum number required would be 3 schools in each center with 250 students in each school. The intraclass correlation is assumed to be 0.05. The sample size of 7500 students from 30 schools located in 5 centers has 90% power to detect a mean between-group difference in BMI of 0.7 units with an effect size of 0.64. Statistical significance is set at 5% (two-sided). Another 2250 students from 9 schools are randomly chosen only for cost-effect analysis, 3 schools for nutrition intervention, 3 schools for physical activity intervention and another 3 schools are treated as control schools.

Intervention

Three interventions will be included in present study: nutrition education, physical activity intervention and comprehensive intervention, the detail strategies are shown in Table 1.

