Initially, the descriptive statistics will be calculated for all variables considered. Anthropometric measurements at baseline will be compared between intervention and control groups using multivariate regression analysis with age and sex in the model. The effects of intervention will be analyzed using mixed procedure, with BMI changes from baseline as the primary outcome variable. The fixed effects include baseline BMI, age, sex, and the intervention group. The schools within center will be treated as a random effect variable. Similar mixed models will be constructed for other outcome variables, including weight, height, BMI z score, fat free mass, fat mass, percent body fat, physical fitness, as well as the chronic disease factors including glucose, insulin, TG, TC, HDL, LDL and blood pressure.

The intervention effect on body composition will be compared according to the real diet and physical activity changes while the intervention effect on chronic disease factors will also be compared between students whose BMI z score increased or not.

Both cost-effectiveness and cost-benefit will be economically analyzed to compare the three strategies, including nutrition education intervention, physical activity intervention and the comprehensive intervention.

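### Comprehensive versus either single-component strategy is a between-centre, non-randomised comparison; the protocol neither plans an indirect comparison nor states the limitation

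*Protocol*

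**What the plan says.** The Objective section of the protocol sets as second purpose to "compare the cost-effectiveness of the comprehensive intervention strategy with two other interventions", one based on nutrition education only and one on physical activity only.

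Study design fixes where each strategy is delivered. Outside Beijing, "Both nutrition education and physical activity intervention will be implied in all intervention schools of 5 cities"; by contrast, "in Beijing, nutrition education intervention will be implied in 3 schools and physical activity intervention among the other 3 schools". Participants describes the allocation: "The first step is that randomly selected 6 schools from each centre assigned to either intervention (3 schools"), with the other three as controls. No step allocates schools between the comprehensive and a single-component strategy.

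Sample size calculations separates two parts. For the main effect, "The sample size of 7500 students from 30 schools located in 5 centers has 90% power". For the economic question, "Another 2250 students from 9 schools are randomly chosen only for cost-effect analysis": three nutrition schools, three activity schools, and "another 3 schools are treated as control schools". None of the nine is a comprehensive school, and their location is not given.

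Analysis strategy states: "Both cost-effectiveness and cost-benefit will be economically analyzed to compare the three strategies". It does not say through which contrasts. The mixed model described there, for BMI change and the other outcome variables, has baseline BMI, age, sex and group as fixed effects and a random effect for schools within centre.

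**The concern.** For comprehensive versus either single-component strategy, strategy and place coincide. A difference between the comprehensive schools and the Beijing nutrition schools is the strategy effect plus whatever separates Beijing from the other centres: the underlying BMI trend, the pupils, the quality of delivery, wages and prices. Randomisation within a centre does not balance these across centres. One strategy could look more effective or more cost-effective because of where it was delivered. The second objective names exactly this comparison, in a trial described as randomised, and no sentence warns the reader.

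**Working it through.** **1. The plan's own figures.**
- Pupils: 7500 + 2250 = 9750, which is 30 + 9 = 39 schools of 250. This agrees with the total under Participants. Six centres of six schools would give 36 × 250 = 9000.
- SD implied by a difference of 0.7 and an effect size of 0.64: 0.7/0.64 = 1.094 kg/m2.
- Design effect: 1 + (250 − 1) × 0.05 = 13.45.
- For 90% power at two-sided 5%, 52 pupils per arm × 13.45 = 699, or 2.8 schools, rounded up to 3. Three schools per arm give 92% power (normal approximation). Fifteen per arm give over 99.9%. The stated 90% therefore fits one centre better than all 7500 pupils. The present point does not depend on this.

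**2. Layout by centre.**

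| Centre | Comprehensive | Nutrition | Activity | Control |
|---|---|---|---|---|
| Each of 5 centres outside Beijing | 3 | 0 | 0 | 3 |
| Beijing, by Study design and Participants (6 schools) | 0 | 3 | 3 | none left |
| Beijing, by Sample size calculations (9 schools) | 0 | 3 | 3 | 3 |

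Placing the nine schools in Beijing is an inference: the other 30 are in five centres, and Study design names Beijing for the single-component strategies.

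**3. What can be estimated.** Take a school-level model with six centre effects and three strategy effects (nine parameters).
- With three Beijing controls (39 schools) the rank is 9 of 9. Comprehensive minus single-component is estimable, as the difference of two within-centre contrasts with control.
- Without them (36 schools) the rank is 8 of 9. Raising the Beijing effect and lowering both single-component effects by the same amount leaves the fit unchanged, so comprehensive minus single-component is not estimable.
- Nutrition minus activity is estimable within Beijing either way.

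**4. Precision of the indirect contrast** (SD 1.094, ICC 0.05, normal approximation).
- Variance of a school mean: 1.094² × 13.45/250 = 0.0644.
- Comprehensive v control, 15 v 15 schools: SE = √(0.0644 × 2/15) = 0.0926.
- Nutrition (or activity) v control in Beijing, 3 v 3 schools: SE = √(0.0644 × 2/3) = 0.207.
- Difference of the two: SE = √(0.0926² + 0.207²) = 0.227.
- Detectable with 90% power: (1.96 + 1.28) × 0.227 = 0.74 kg/m2.
- Power for 0.7: Φ(0.7/0.227 − 1.96) = Φ(1.12) = 87%. For 0.35, an assumed increment of half that size: Φ(1.54 − 1.96) = Φ(−0.42) = 34%.
- An unadjusted direct comparison of 15 with 3 schools would show SE = √(0.0644 × (1/15 + 1/3)) = 0.160. It looks tighter only because it leaves out the centre difference.

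**5. Illustration of the possible distortion.** The protocol gives no between-centre variance, so shares of 1%, 2.5% and 5% of total variance are assumptions. With identical strategies, the chance difference between Beijing and the mean of five other centres has SD = 1.094 × √(share × (1 + 1/5)) = 0.12, 0.19 and 0.27 kg/m2. The false-positive rates below come from 20,000 simulated trials of an assumed four-group, 39-school analysis without a centre term (pooled school variance, 35 df), at a nominal 5%.

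| Centre share | School share | Comprehensive v nutrition | Nutrition v pooled control |
|---|---|---|---|
| 0.01 | 0.04 | 9.7% | 8.0% |
| 0.025 | 0.05 | 13.4% | 10.1% |
| 0.05 | 0.05 | 18.4% | 13.5% |

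These rates describe the assumed model, not an analysis that the protocol specifies.

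**The case against.** The strongest defence has four parts.

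- **The economic part has its own controls.** This fits an intention to compare each strategy with local controls, and the choice of estimator could be left to a statistical analysis plan that is not at hand. It stands in part: the protocol does not prescribe a pooled analysis, and its silence should not be read as one. But the layout and the objective are fixed in the protocol. A later document can choose the estimator; it cannot make the comparison randomised.
- **Not all three strategies are affected.** A reader might infer that every comparison among them is inseparable from centre. The documents do not support that. Nutrition versus activity is made within Beijing, and with Beijing controls the other two contrasts are estimable indirectly.
- **The absence of a centre term is not established.** The random-effect sentence under Analysis strategy can be read with or without a centre component. A reader might also take the 8% to 18% false-positive rates as the trial's own. They are not, because the economic comparison is stated without any model or test.
- **Local controls do not cure everything.** According to Table 1 they receive no intervention, so a strategy's incremental cost is essentially its whole local cost, and subtracting controls leaves price and wage differences in place. This stands and shapes the fix.

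**Conclusion.** The point holds for comprehensive versus nutrition only and comprehensive versus activity only. Both are between-centre, non-randomised comparisons, and the protocol neither plans an indirect comparison nor states the limitation.

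Done through local controls, the contrast can reliably detect only about 0.74 kg/m2, slightly more than the whole comprehensive-versus-control difference of 0.7 for which the trial was sized. This rests on the SD implied by the protocol, its ICC of 0.05, a normal approximation that is optimistic with three schools per arm, and three control schools in Beijing. It also assumes no strategy-by-centre interaction, which the design cannot test for this contrast, because no comprehensive school is in Beijing.

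A reader might infer that the main result or the policy aim is undermined. The documents do not support that: the primary comparison of comprehensive with control is made within the five other centres and is unaffected, and the Objective section does not tie the policy recommendations to the comparison between strategies.

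**What to change.** 1. Reconcile Study design and Participants (six schools per centre; in Beijing, three nutrition and the remaining three activity) with Sample size calculations (nine schools, three of them controls). If the three controls are in Beijing, say so. If they are not, the contrast between comprehensive and single-component strategies cannot be estimated with centre in the model, and the objective must be cut back.
2. In Analysis strategy, estimate each strategy's incremental BMI effect and incremental cost only against control schools in the same centre or centres. Do not pool controls across centres without a centre term.
3. Compare comprehensive with each single-component strategy as an anchored indirect comparison of those increments, with school-level uncertainty: add the two variances, or bootstrap schools within centre and arm.
4. Value resources at common unit prices across centres. This requires quantities (teacher hours, training sessions, materials, travel) to be recorded as well as local spending.
5. State in the Objective that this comparison is indirect and non-randomised and assumes no strategy-by-centre interaction.

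The cost is wording, some extra analysis and the recording of quantities. No school or intervention changes. The interval for the strategy contrast widens (SE 0.227 instead of an apparent 0.160), and the claim for the second objective becomes weaker.

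### The stated 90% power for 30 schools does not follow from the protocol's own inputs, which give more than 99.9%

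*Protocol*

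**What the plan says.** Everything needed to check the power is in the protocol, mostly under Sample size calculations.

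- Sizing variable: "The variable used for the calculation of sample size is the BMI changes".
- Target: a difference of 0.7 kg/m2, given again as "a mean between-group difference in BMI of 0.7 units with an effect size of 0.64".
- Clustering: "The intraclass correlation is assumed to be 0.05".
- Test: two-sided, 5%.
- Minimum: "the minimum number required would be 3 schools in each center with 250 students in each school". This sentence does not say whether the three schools are per arm, and it attaches no power to them.
- Power: "The sample size of 7500 students from 30 schools located in 5 centers has 90% power".

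Under Participants, allocation within a centre is described as "randomly selected 6 schools from each centre assigned to either intervention (3 schools) or control condition". Over five centres that makes 15 schools against 15.

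Under Analysis strategy, the primary analysis is a single mixed model for BMI change, with one intervention effect and schools within centre as random. That comparison is pooled over centres.

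**The concern.** The same section calls three schools per centre enough to detect 0.7 kg/m2, then gives only 90% power for the same difference to 30 schools. If the minimum is per arm within a centre, the full design has five times as many schools in each arm. Power cannot then be close to the level that justified the minimum.

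At stake is what the document tells its reader about the trial's sensitivity. From the text it is unclear whether the powered comparison is one centre or the pooled trial. The difference quoted as detectable with 90% power is also more than twice the one the pooled design can detect (0.7/0.31 = 2.3).

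**Working it through.** **Inputs.** Difference 0.7 kg/m2, effect size 0.64, intraclass correlation 0.05, 250 per school and two-sided 5% come from Sample size calculations. The 3-to-3 allocation per centre comes from Participants. No SD is stated. Reading 0.64 as the difference divided by the SD of individual BMI change gives SD = 0.7/0.64 = 1.094.

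**1. Design effect.** 1 + (250 − 1) × 0.05 = 13.45.

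**2. The plan's figure: 15 against 15 schools.** Students per arm: 15 × 250 = 3750.

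- SE = 1.094 × √(2 × 13.45/3750) = 0.0926 kg/m2.
- Noncentrality = 0.7/0.0926 = 7.56.
- Power is above 99.99% by the normal approximation, and also by a t test on 28 df (30 − 2) or on 24 df (stratified by five centres). Even on 4 df it is 99.96%.

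The stated 90% does not reproduce.

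**3. What 15 against 15 detects with 90% power.**

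- Normal: (1.960 + 1.282) × 0.0926 = 0.30 kg/m2.
- t, 28 df: (2.048 + 1.313) × 0.0926 = 0.31 kg/m2, or 0.31/1.094 = 0.28 SD.

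**4. What would make 90% true for 30 schools (t, 28 df).** Changing one input at a time, either of these would do:

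- An intraclass correlation of about 0.27. The design effect is then 1 + 249 × 0.27 = 68.2, the noncentrality 3.36 and the power 89.9%.
- An SD of about 2.47, that is, an effect size of 0.28.

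Both contradict the stated inputs.

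**5. Where 90% may come from: 3 against 3 schools in one centre.** Normal-approximation requirement at 90% power:

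- Per arm without clustering: 2 × (1.960 + 1.282)²/0.64² = 51.3.
- With clustering: 51.3 × 13.45 = 690 students; 690/250 = 2.76 schools, rounded up to 3.

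Power by number of schools per arm, normal approximation: 79% with 2 and 92% with 3. Three is therefore the smallest whole number that reaches 90%, which matches the stated minimum. For 3 against 3, SE = 1.094 × √(2 × 13.45/750) = 0.207 and noncentrality = 3.38. Power depends on the method:

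| Method, 3 against 3 | Power for 0.7 kg/m2 |
| --- | --- |
| Normal approximation | 92% |
| t test, 4 df (6 schools − 2) | 72% |

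**6. Other reading of the minimum.** If three schools per centre were the total over both arms, five centres would have 15 schools, on average 7.5 per arm. Power would be 99.96% (normal) or 99.8% (t, 13 df). That does not give 90% either.

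**7. Losses.** The protocol gives only an approximate 250 per school. As an assumption of this check, take 200 analysed per school: design effect 1 + 199 × 0.05 = 10.95, SE = 1.094 × √(2 × 10.95/3000) = 0.0935, noncentrality 7.49. The conclusion does not move, because the number of schools drives the precision.

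**The case against.** The strongest reply is that the error is harmless. The primary comparison has more power than stated, nobody would enrol differently, and no planned analysis depends on the 90%. That stands, and it limits how serious the point is. It does not make the figure right.

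Several stronger conclusions are tempting, but the protocol does not support them.

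- **That the 90% is the one-centre figure.** A reader might infer this, and the match in step 5 makes it likely. The protocol does not state it, and the forward power for 3 against 3 is 92% by the normal approximation, not 90%.
- **That the trial has only 72% power.** The 72% needs a t test on 4 df. That is the sounder method with six clusters, but the protocol states no degrees of freedom. It also concerns a per-centre BMI comparison that Analysis strategy does not plan.
- **That the minimum is a false claim of 90% power per arm.** The sentence mentions neither arms nor power, so it contains no such claim to remove.
- **That the nine additional schools are shown to be underpowered.** They are set aside for cost-effect analysis and carry no stated power. Nothing in the text ties the three-school minimum to them.
- **That a true effect of 0.3 to 0.6 kg/m2 would be dismissed.** Nothing under Analysis strategy makes interpretation depend on 0.7.

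**Conclusion.** The 90% is wrong as stated for 30 schools. On the protocol's own inputs, power for 0.7 kg/m2 exceeds 99.9% under every method tried, and the difference detectable with 90% power is about 0.31 kg/m2 (0.28 SD). This rests on 15 schools per arm and on reading 0.64 as a difference divided by the individual SD of change, so the SD of 1.09 is back-calculated rather than stated.

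A one-centre origin for the 90% is probable but unproven. The error understates the power of the pooled primary comparison and alters neither enrolment nor analysis. It is a figure to correct, not a defect that must be mended before the trial can proceed.

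**What to change.** In Sample size calculations:

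1. Replace the 90% statement with the pooled figure: 15 against 15 schools give more than 99% power for 0.7 kg/m2 or, equivalently, 90% power for about 0.31 kg/m2. Print the SD of change (1.09, marked as implied by 0.7/0.64 unless the authors have a sourced value), intraclass correlation 0.05, 250 per school and the degrees of freedom (28, or 24 if stratified by centre; both give about 0.31).
2. State that the powered comparison is the pooled one in Analysis strategy.
3. If the three-school minimum is kept, say whether it is per arm and label its power by method: 92% by the normal approximation, about 72% by a t test on 4 df.

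If the authors used a different SD, intraclass correlation or formula, they should print it and recompute. The cost is a few sentences of protocol wording, with no change to enrolment, allocation or the planned model.

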**Table 1 Contents of interventions**

| Group | Interventions |
| --- | --- |
| control group | No intervention |
| Physical activity intervention group | 1. "Happy 10" campaign(2 times/day 10 minutes/time or 1 time/day 20 minutes/time)  2. Parents , health workers / health education teacher: "happy 10" training. |
| Dietary intervention group | 1. Students take part in "Nutrition and Health" classes  2. Parents participate. in "nutrition and health" classes. Give parents corresponding publicity materials.  3. Teacher, health / health education teacher participate in "nutrition and health" classes. Give them corresponding publicity materials.  4.School canteen managers, operators, competent leadership and staff room participate in "nutrition and health" classes.  5. Give them corresponding publicity materials. |
| Comprehensive (Dietary & Physical activity) intervention group | Happy 10+nutrition education  1. Students take part in "Nutrition and Health" classes  2. "Happy 10" campaign(2 times/day 10 minutes/time or 1 time/day 20 minutes/time  3. Parents participate. in "nutrition and health" classes. Give parents corresponding publicity materials.  4. Teacher, health / health education teacher participate in "nutrition and health" classes. Give them corresponding publicity materials. And give them a "happy 10" training.  5. School canteen managers, operators, competent leadership and staff room participate in "nutrition and health" classes. |

**Staff Training**

Staffs from National Institute for Nutrition and Food Safety, Chinese CDC had trained the study group members from the cooperation center for five days. Teachers, usually classroom tutors and/or health educators, will attend a two-days training session conducted by the staff of their center with the training slides and videos provided by Chinese CDC. They could learn how to integrate the program into the school curriculum, and how to perform the activities. Slides and videos about nutrition, childhood obesity, risk factors, health consequences, and prevention will be prepared by Chinese CDC and provided to school teachers. Teachers model the lessons to ensure that they understood the recommended techniques and strategies for implementation.

**Outcome measures**

Measurements will be collected in the summers of 2009 (baseline) and in summer 2010 (intervention). Children will be fasted the night before and measured the next morning by trained research staff. Consistent assessment methods will be used throughout the study.

Tables 2 Description of outcomes

| Name of Outcome | Category of Outcome | Description |
| --- | --- | --- |
| Physical examination | Primary outcome | Height, weight, waist circumference, blood pressure |
| Body Composition | Primary outcome | Bioelectrical impedance, single-standard Water Law |
| Blood biochemical indices | Primary outcome | Blood glucose, blood cholesterol, blood triglycerides, blood high-density lipoprotein, low density lipoprotein in blood, blood insulin |
| Dietary intake situations | Primary outcome | 24-hour record of 3 days dietary questionnaire |
| Physical activities | Primary outcome | Seven days of physical activity recall questionnaire, wearing the energy monitoring device, a 24-hour physical activity record sheet |
| Physical measurements | Primary outcome | Standing long jump, 50 m, 50 m × 8 from the run |
| School basic conditions | Secondary outcome | Number of students, the class distribution of the floor, the school's facilities and equipment, sports arrangements, nutrition-related staffing, students in the school dining situation |
| Obesity-related knowledge, attitudes and practices | Primary outcome | Primary school students questionnaire, parents questionnaire, teacher questionnaire, food service personnel questionnaire |
| Cost | Primary outcome | Cost related to intervention material, training, supervisor, teachers time input, transportation, |

Analysis strategy

Initially, the descriptive statistics will be calculated for all variables considered. Anthropometric measurements at baseline will be compared between intervention and control groups using multivariate regression analysis with age and sex in the model. The effects of intervention will be analyzed using mixed procedure, with BMI changes from baseline as the primary outcome variable. The fixed effects include baseline BMI, age, sex, and the intervention group. The schools within center will be treated as a random effect variable. Similar mixed models will be constructed for other outcome variables, including weight, height, BMI z score, fat free mass, fat mass, percent body fat, physical fitness, as well as the chronic disease factors including glucose, insulin, TG, TC, HDL, LDL and blood pressure.

The intervention effect on body composition will be compared according to the real diet and physical activity changes while the intervention effect on chronic disease factors will also be compared between students whose BMI z score increased or not.

Both cost-effectiveness and cost-benefit will be economically analyzed to compare the three strategies, including nutrition education intervention, physical activity intervention and the comprehensive intervention.

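### Table 2 labels eight of nine outcome domains primary and omits BMI, while the sample size and analysis sections rest on BMI change as the single primary outcome

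*Protocol*

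**What the plan says.** Three places in the protocol bear on the primary outcome.

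- **Sample size calculations.** One variable is used: "The variable used for the calculation of sample size is the BMI changes". The level is given once, here: "Statistical significance is set at 5% (two-sided".
- **Analysis strategy.** The intervention effect is estimated in a mixed model "with BMI changes from baseline as the primary outcome variable". Similar models are then announced for other outcomes. The list is open-ended and names weight, height, BMI z score, fat free mass, fat mass, percent body fat, physical fitness, glucose, insulin, TG, TC, HDL, LDL and blood pressure.
- **Outcome measures, Table 2.** Of nine rows, eight carry the primary label: physical examination, body composition, blood biochemistry, dietary intake, physical activities, physical (fitness) measurements, knowledge/attitudes/practices, and cost. Two of these rows read "Physical examination | Primary outcome | Height, weight, waist circumference, blood pressure" and "Dietary intake situations | Primary outcome | 24-hour record of 3 days dietary questionnaire". Only school basic conditions is secondary. BMI has no entry; its components, height and weight, do.

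**The concern.** The main objective includes evaluating the effectiveness of the comprehensive programme, so the protocol has to say which result settles that. Two sections say BMI change. The table that formally classifies the outcomes spreads the primary label over eight domains and does not put BMI change among them by name.

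If BMI change showed no effect but a lipid, a fitness test or a body composition measure did, the investigators could call the second result primary by pointing to Table 2, or not primary by pointing to the Analysis strategy. The choice could be made after the data are seen. The 5% level stated for the BMI comparison would then no longer describe the chance of a false claim of effectiveness.

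**Working it through.** **1. What the trial is sized on.** Inputs from Sample size calculations: "has 90% power to detect a mean between-group difference in BMI of 0.7 units with an effect size of 0.64", "The intraclass correlation is assumed to be 0.05", 250 students per school, two-sided 5%.

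- Implied SD: 0.7 / 0.64 = 1.094 kg/m².
- Design effect: 1 + (250 − 1) × 0.05 = 13.45.
- Students per arm before clustering: 2 × (1.960 + 1.282)² / 0.64² = 51.3.
- With clustering: 51.3 × 13.45 = 690 students, and 690 / 250 = 2.76, so 3 schools per arm.

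This matches the stated minimum, "the minimum number required would be 3 schools in each center with 250 students in each school". With exactly 3 schools per arm, the power is 92.2% by the normal approximation. With all 7500 students (15 schools per arm), the same inputs give more than 99.99%, so the stated 90% does not reproduce for that total. That mismatch is a separate matter and nothing below depends on it. What counts here is that the calculation has one outcome, BMI change.

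**2. Table 2 set against the Analysis strategy.**

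| Outcome | Table 2 | Analysis strategy |
| --- | --- | --- |
| BMI change | not listed | the primary variable |
| Height, weight, blood pressure | in a primary row | further outcome |
| Fat free mass, fat mass, percent body fat | in a primary row (body composition, listed by method) | further outcome |
| Fitness | in a primary row (three tests) | further outcome |
| Glucose, insulin, TG, TC, HDL, LDL | in a primary row | further outcome |
| BMI z score | not listed | further outcome |
| Waist circumference, diet, physical activity, knowledge/attitudes/practices | in a primary row | not named as a modelled outcome |
| Cost | primary | economic analysis |

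The same measures are primary in one section and not in the other.

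**3. Size of the ambiguity, as an illustration.** Count only outcomes that are both in a primary row and named for a mixed model, taking fitness and blood pressure once each: 3 (height, weight, blood pressure) + 3 (body composition) + 1 (fitness) + 6 (blood) = 13.

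Suppose there is no true effect, each outcome is tested at 5%, and any one significant result is read as a primary success. Under independence:

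- 13 outcomes: 1 − 0.95^13 = 1 − 0.513 = 48.7%.
- One test in each of the seven non-cost primary domains: 1 − 0.95^7 = 1 − 0.698 = 30.2%.
- BMI change alone: 5%.

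These outcomes are correlated, so the true figures would be lower. In the extreme case of perfect correlation, both would fall to 5%.

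**The case against.** The best defence is that the protocol already fixes one primary outcome. The sample size and analysis sections agree on BMI change. Table 2 lists instruments and methods, such as bioelectrical impedance or a recall questionnaire, and reads like an inventory of data collection with loose labels. Height and weight, from which BMI is computed, are in its first row. Rules for multiplicity and full lists of tested outcomes are often left to a statistical analysis plan, which may exist.

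Much of this stands, and it rules out three stronger readings.

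- A reader might infer that every measure is tested at 5%. The protocol does not say so. The level appears once, in the sample size section. Waist circumference, diet, physical activity and the questionnaires are not named for a model, though the open-ended list does not exclude them, and cost goes to an economic analysis.
- A reader might count every non-cost entry in the primary rows (4 + 2 + 6 + 1 + 3 + 3 + 4 = 23) and give 1 − 0.95^23 = 69% as the trial's error rate. That count mixes endpoints with methods, devices and questionnaires, and 9 of the 23 entries (waist circumference 1, diet 1, activity 3, questionnaires 4) have no stated test.
- A reader might conclude that success on any one measure makes the trial positive. No such rule is written.

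The absence of a multiplicity rule is likewise no fault in a protocol read without its analysis plan.

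The defence does not remove the contradiction. A reader can guess that the table is loosely labelled, but its labels are explicit and nothing in it ranks BMI change first. An analysis plan could choose one section over the other; it could not make both true.

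**Conclusion.** The point holds as a contradiction within the protocol about which outcome decides effectiveness. Table 2 labels eight of nine domains primary without naming BMI, whereas the sample size and analysis sections rest on BMI change alone. This can be read directly from the page and depends on no assumption.

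The size is illustrative only. The false-positive chance would be about 49% over the 13 outcomes that both sections cover, or about 30% over seven domains. Both figures assume independence, a 5% test of each outcome, and a reading of Table 2 in which any single significant result counts as a primary success. The protocol permits that reading by its labels but does not state it. Correlation lowers both figures. They show what the ambiguity could cost; they are not the trial's error rate.

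The conflict should be resolved before outcome data are analysed, because it concerns the main conclusion and is easily removed.

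**What to change.** Edit Table 2 to agree with the Sample size calculations and the Analysis strategy:

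- Add BMI change from baseline (summer 2009) to summer 2010, derived from height and weight, as the single primary outcome.
- Relabel the other rows secondary.
- Assign cost to the secondary, economic objective.
- State in the Analysis strategy that the effectiveness conclusion rests on BMI change at two-sided 5%.

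The cost is the relabelling of one table and one added sentence. Data collection, sample size and the planned models stay as they are. What is given up is the option of presenting another measure as a primary result.
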